Following screening, 60 patients presenting MRSE (assessed by a standardized questionnaire; see **Appendix 3, questionnaire 3**) under statin monotherapy (any statin, any dosage) as well as 30 patients without MRSE under statin monotherapy (paired for statin and dosage with the MRSE cohort) will be evaluated. Muscle strength and fatigability will be tested by standardized procedures before and after two months of stopping statin monotherapy. Briefly, strength of the extensors and flexors muscles of the dominant leg will be quantified with a Biodex isokinetic dynamometer available in our research centre. Forces will be tested during 3 reps at 60 and 180 deg/sec and endurance during a 15 reps test at 180 deg/sec. These tests will be preceded by a 5 reps warm-up at 60 deg/sec including one movement at maximal voluntary contraction [46]. Each maximal concentric contraction will be performed in the first 90 degrees of the knee range of motion. Patients will sit in an upright position and mechanical axis and resistance pads will be aligned according to the manufacturer's guidelines. The results will be reported in Newton-meters (Nm). Peak torque, rate of torque development and total work values will be obtained following these isometric and isokinetic measurements. These groups of muscles were selected because muscle weakness or myalgias with statins are most frequently localized in lower limbs. Handgrip strength of the dominant hand will also be tested in a static mode with a Jamar dynamometer (best of 3 repetitions). These testing procedures are well standardized, easy to perform and very reproducible, and are routinely used in the department of physical therapy at our centre. Test-retest variability for the Biodex measurements is shown to be within  $\pm 15\%$  [46], which our personal experience confirms. The primary efficacy parameter will be the percent change for these measurements from baseline to end of each phase of the study.

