In the experimental group (n=45; 30 with MRSE under statin monotherapy, 15 without MRSE under statin monotherapy from objective #1), statins will be reintroduced following one month of oral vitamin D supplementation (Vitamin D3 [cholecalciferol], Laboratoire Riva Inc., Blainville, Québec; 4 x 10,000 IU/week, 40,000 IU/week total). This falls within the range of average daily dosage used in the studies of Lee *et al.* [44] and Ahmed *et al.* [43] that showed relief from myalgia and allowed statin reintroduction in patients with low serum 25(OH)D levels. This also falls within the generally acceptable upper limit of daily vitamin D intake, the “no observed adverse event level” being 10,000 IU per day, and well below the “lowest observed adverse event level” of 40,000 IU per day (as discussed in [45]). Patients will be rechallenged with the same statin and at the same dose they were taking at the onset of objective #1. Patients will continue to supplement with vitamin D during the statin rechallenge period, which will last for a maximum of 2 months. The patients may request at any time over this period the cessation of statin therapy if they consider any reappearance of MRSE to be too severe to continue. Based on the clinical experience of [name] (co-PI), patients rarely develop muscle symptoms in less than 2 weeks following statin introduction.

In the control group (n=45; 30 with MRSE under statin monotherapy, 15 without MRSE from objective #1), no vitamin D supplementation will take place prior to statin reintroduction, subjects receiving instead a placebo provided by the pharmacy service of the CHUL. Placebo supplementation will also continue following statin reintroduction (1 month after the start of the RCT). Readers are referred to figure 1 and table 1 for more details on patient assignment.

Participants will be asked by the study coordinator, by phone, a few days before their visits at 4 weeks after randomization and at end-of-trial, to bring their bottles of capsules for their visit to the CHUL. The pharmacy will then check their apparent compliance by counting the remaining capsules and surveying the participants on their supplementation practices. A compliance rate of at least 80% will be required for successful outcome in the trial.

The changes in 25-OH vitamin D, calcium, phosphate, alkaline phosphatase, and parathyroid hormone, from baseline to end of each phase of study will be studied in all patients to evaluate the

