### Research Proposal

impact of stopping statin monotherapy and the rechallenge of statin monotherapy under vitamin D repletion. As described in objective #1, and for both groups, muscle strength and fatigability tests and venous punctures (particularly for 25-OH vitamin D level assessments) will be obtained immediately prior to statin reintroduction (after one month of vitamin D or placebo). These and muscle biopsies will also be taken at the end of the statin-reintroduction period (within 1 week of the maximum 2 months trial length or from when patients cease statin use due to reappearance of important MRSE).

Muscle biopsies of the *vastus lateralis* will be obtained for 30 of these patients: 10 presenting MRSE and receiving vitamin D, 10 presenting MRSE and not receiving vitamin D, 5 without MRSE and receiving vitamin D, and 5 without MRSE and not receiving vitamin D. These will be the same patients that had biopsies in objective #1, allowing us to evaluate changes to skeletal muscle tissue over time. Our laboratory has extensive experience in multiple biopsies from the same patient over time, and we have published numerous papers using this approach (e.g., [49, 53-57]).

In addition to the testing and questionnaires outlined in Figure 1, phone interviews will be performed every 2 weeks during the RCT to assess adverse events. An adverse event is any untoward medical occurrence in a study subject that is temporally associated with the use of a medicinal product, regardless of its potential relationship to the medicinal product. An adverse event, therefore, can be any unfavorable or unintended sign, symptom or disease (new or exacerbated), whether or not related to the study drug. The severity of an adverse event will be scored according to the following scale:

Mild: Awareness of sign or symptom, but easily tolerated

Moderate: Discomfort enough to cause interference with usual activity

Severe: Incapacitating with inability to perform usual activities

Participants will be provided with the adverse event guide presented in **Appendix 3** to help classify the nature and intensity of adverse events during phone interviews and in questionnaires.

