Participants will be required to provide informed consent, will be assured confidentiality and will be offered the possibility to withdraw from the study at any time and without justification. Premature withdrawals and their causes will be carefully documented. Subjects who withdraw before the required sample size has been attained will be replaced; those who withdraw after the required sample size has been attained will not be replaced.

**EXPECTED FINDINGS AND OUTCOMES.** *This second phase of the proposal will allow us to confirm that MRSE suffering patients may be protected against statin-induced myalgia as well as for muscle function and biological markers of muscle cell degeneration after vitamin D supplementation. In addition, these data will demonstrate a significantly improved capacity to achieve lower LDL-cholesterol levels in cardiovascular prevention while reducing the risk of muscle side-effects from statin use.*

Primary outcomes for this objective include: (1) reduced functional impact of statins on muscle strength and endurance in the vitamin D supplemented group, and (2) a greater tolerance of statin reintroduction (i.e., fewer self-reported MRSE) in the group receiving vitamin D supplementation; secondary outcomes will be (3) the normalization of muscle histological, ultrastructural, and mitochondrial (metabolic) abnormalities with vitamin D supplementation and (4) the demonstration of improved statin tolerance with vitamin D supplementation regardless of initial 25(OH)D status.

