## **5.0 STATISTICAL ANALYSES**

Although there are no published data on the loss of muscle force in humans following statin treatment, experiments using men with coronary artery disease showed that  $n = 10$  to  $20$  is sufficient to distinguish differences between groups [58]. Based on the high accuracy of the Biodex apparatus and our preliminary data, we calculate that a total of 60 MRSE suffering patients will be sufficient to demonstrate effects on muscle function by statin withdrawal or vitamin D supplementation (30 per group, one with vitamin D, the other with placebo - see APPENDIX 3 for Power Calculations). These sample sizes are similar to those producing data showing reversible myositis-myalgia in statin-treated low serum 25(OH)D patients receiving vitamin D repletion [43, 44]. For biopsies, the number of subjects in each study group was determined based on our previous work (*e.g.*, [49]), biopsy feasibility and the availability of patients from our clinic [59]. From the patient case reports documented with some of these MRSE and considering the analytical precision of the methods proposed, we are confident that we will show statistically significant differences between MRSE suffering and not suffering patients [13].

Statistical analyses will test the comparison of subgroups (with/without symptoms and with/without vitamin D repletion) on the percent change from baseline (end – baseline) of specific measurements. Changes from baseline (end – baseline) of all clinical muscle symptoms will be also analyzed. Normal distribution of fasting marker levels will be examined and, if necessary, they will be normalized by transformation prior to statistical analyses in order to reduce the skewness of their distribution. One-way ANOVA will be used to compare means of continuous variables. Differences in proportions (*e.g.* proportion of patients having increments in one or more specific markers) will be compared using either the Chi-square test, or the Fisher's exact test when appropriate. Statistical analyses will be performed using SAS (SAS Institute Inc.) and/or JMP (SAS Institute Inc.) software. All tests will be two-tailed and considered statistically significant when alpha level  $< 0.05$ .

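### The Objective #2 muscle-function comparison uses no covariate, although two strength tests per patient precede randomisation; the test is valid but gives up power, by an amount the protocol does not allow one to fix

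*Protocol*

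**What the plan says.** Objective #1 provides two functional tests before anyone is randomised: "Muscle strength and fatigability will be tested by standardized procedures before and after two months of stopping statin monotherapy". In Objective #2 patients are randomised to vitamin D or placebo, and after one month the statin returns: "Patients will be rechallenged with the same statin and at the same dose they were taking at the onset of objective #1". A further test is "obtained immediately prior to statin reintroduction (after one month of vitamin D or placebo"), and the last comes at the end of rechallenge. The first primary outcome of Objective #2 is "reduced functional impact of statins on muscle strength and endurance in the vitamin D supplemented group".

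For the analysis, section 5.0 states: "Statistical analyses will test the comparison of subgroups (with/without symptoms and with/without vitamin D repletion) on the percent change from baseline". It adds: "One-way ANOVA will be used to compare means of continuous variables". No covariate is named. Randomisation is stratified on MRSE status, 25(OH)D, age and sex, but not on muscle strength. Baseline is not defined for Objective #2. The nearest wording, under Functional assessment and blood samples, is by phase: "The primary efficacy parameter will be the percent change for these measurements from baseline to end of each phase of the study".

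**The concern.** The first two tests together estimate how much strength a given patient loses on a given statin and dose. The rechallenge repeats that exposure. If the loss repeats even partly, the pre-randomisation pair predicts the outcome. A percent change uses only one earlier value, so under the stated analysis that predictable part stays in the error term.

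Power is at stake, not validity. The preliminary SDs are large (28 to 64%) against a stated test-retest variability within ±15%, and there are only 30 MRSE patients per arm. The cost would be felt most if vitamin D protects only partly.

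**Working it through.** **Inputs.**
- Two-sided alpha 0.05 and 30 v 30 MRSE patients (section 5.0).
- Preliminary withdrawal changes in 9 patients, extensors then flexors (Preliminary data): strength 22±43% and 17±28%; power 28±64% and 29±41%; endurance 28±57% and 20±35%.
- Test-retest variability ±15% (Functional assessment), read here as the SD of a change. That reading is an assumption.
- Repeatability ρ, the correlation between a patient's first and second statin effect. The documents do not give it, so 0, 0.3, 0.5 and 0.8 are shown.

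**The plan's own figure.** The power calculation sits in an appendix that is not shown, and the text gives neither a target power nor a vitamin D effect, so 30 per group cannot be formally reproduced. With the extensor-strength figures and 80% power assumed:
- paired test of withdrawal: n = (43 × (1.96 + 0.84)/22)² ≈ 30 patients;
- two-arm comparison with common SD 43: about 60 per arm.

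**Unadjusted power, extensor strength, 30 v 30, full protection.**
- Common SD in both arms: SE = 43 × √(2/30) = 11.1; 22/11.1 = 1.98; power 51%.
- Protection also removes the spread of statin effects in the vitamin D arm: SE = √((43² + 15²)/30) = 8.3; 22/8.3 = 2.65; power about 75%.

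The simulation below has the second structure, hence its starting value of about 74%.

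**Simulation.** Let B be underlying strength, E1 and E2 the statin effects with correlation ρ, and π the protected share.
- On statin: Y1 = B − E1 + error.
- Off statin: Y2 = B + error.
- End of rechallenge: Y3 = B − (1 − π × arm) × E2 + error.
- Error SD per test is 15/√2 = 10.6. The variance of E is the preliminary SD² − 15²; for extensor strength 1849 − 225 = 1624.

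Three analyses are compared: change from Y2, adjustment for Y2 alone, and adjustment for Y1 and Y2. With 1,500 trials per scenario the simulation error near 75% power is √(0.75 × 0.25/1500), about 1.1 points.

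Change in power from adjusting for both values, across all six measures, full protection:

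| ρ | Change in power (points) |
|---|---|
| 0 | −1 to +1 |
| 0.3 | 0 to +3 |
| 0.5 | +2 to +7 |
| 0.8 | +4 to +15 |

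Selected results at ρ = 0.8:

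| Measure | Protection | Change from Y2 | Both values |
|---|---|---|---|
| Extensor strength | full | 74% | 87% |
| Flexor strength | full | 83% | 92% |
| Extensor power | full | 63% | 78% |
| Flexor power | full | 94% | 99% |
| Extensor strength | half | 23% | 40% |
| Flexor strength | half | 26% | 42% |
| Flexor power | half | 37% | 63% |

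Type I error is 4 to 6%. Adjusting for Y2 alone gains essentially nothing here (extensor strength 74% to 75%), but the model builds this in by drawing E independently of B.

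**Check with a constant benefit and common SD.** The correlation between the withdrawal response and the rechallenge change is r = (ρ × 1624 + 112.5)/1849, and adjustment shrinks the SD to 43 × √(1 − r²).
- ρ = 0.25: r = 0.28, power 54%.
- ρ = 0.5: r = 0.50, SD 37.2, power 63%; for 80% power, 45 per arm instead of 60.
- ρ = 0.75: r = 0.72, power 81%.

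All three compare with 51% unadjusted. A log-scale simulation (assumed statin-effect SD 0.25, vitamin D effect 0.15) gives 48 to 58% unadjusted and 52 to 60%, 58 to 67% and 72 to 85% adjusted at the same three values of ρ. The direction agrees; the size depends on how protection acts.

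**The case against.** *This is an optimisation, not an error.* True as to validity: an unadjusted comparison of randomised arms is sound. A reader might infer that the result would be biased or its type I error inflated; nothing in the documents supports that. Nor does section 5.0 forbid adjustment. But it does fix a method and an outcome variable for this comparison, so the point is more than detail left to a later plan.

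*The on-statin value may not be ignored.* If baseline meant the entry visit, that value would be the denominator. The by-phase wording and the outcome favour the off-statin test but do not settle it. Under the entry-visit reading, power at ρ = 0.8 with full protection was 52 to 88%, against 78 to 99% with both values. On the log scale the gap was small at 0.75 (69 to 83% v 72 to 85%) and wide at 0 (31 to 34% v 49 to 56%). Neither single baseline is reliably better than using both.

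*High repeatability is unproven.* This stands. The on-statin test may follow up to a year of treatment, whereas rechallenge lasts at most two months and can end early. A reader might also infer from 28 to 64% against ±15% that most of the spread is a stable personal statin effect. The figures come from nine uncontrolled patients with one before-and-after pair each. Pain-limited effort, learning or day-to-day variation could produce the same spread without repeating.

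*The model is strained.* Partly true. It treats percentage rises from the on-statin value as additive falls from the off-statin value. For extensor power, effect SD √(64² − 15²) = 62 puts about 12% of patients above a 100-point fall. The log-scale check avoids this and points the same way.

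**Conclusion.** The point holds as one of efficiency. The stated analysis is valid but makes no use of one of two pre-randomisation strength tests that may predict the response to the same statin and dose. Under full protection the gain from using both runs from nothing (ρ = 0), through 0 to 3 points, close to simulation noise (ρ = 0.3), to 4 to 15 points (ρ = 0.8). Under half protection at ρ = 0.8 it is about 12 to 26 points. These figures rest on the nine-patient means and SDs, on ±15% read as an SD, and on a repeatability the protocol does not report, so no single figure should be quoted as the loss.

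Two further inferences are not supported. The match between 30 and the paired extensor calculation does not show that the trial was sized on a paired test, since the power appendix is not shown. The argument also does not carry over to symptoms as such: the in-house questionnaire has three versions across phases, so a common score cannot be assumed. An arm-by-withdrawal-response interaction has no calculation behind it either and is not asked for.

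**What to change.** For each Objective #2 muscle-function outcome, model the end-of-rechallenge value (log scale if skewed) on arm, the on-statin value, the end-of-withdrawal value and the stratification factors. State which visit is baseline for any percent change that is still reported. Do not use the test after one month of vitamin D or placebo as a covariate: it follows randomisation and may already reflect treatment. Apply the same approach to a symptom score only where the same instrument was scored at the on-statin visit.

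Cost: no new visit, measurement or patient. The strength values take one or two degrees of freedom, plus those of the stratification factors. If the statin effect does not repeat, the loss is at most about 1 to 2 points of power.

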**Research Proposal**

---

and risk of falls are mostly observational and in older adults (reviewed in [29-33]). At the muscle cell level, vitamin D deficiency is associated with predominantly type II muscle fiber atrophy (more so in severely deficient patients), enlarged interfibrillar spaces and fat infiltration, fibrosis and glycogen granule accumulation [34].

Whether vitamin D supplementation can itself impact muscle strength or endurance or correct modifications observed with deficiency remains a matter of significant controversy. Studies into this area have mostly been performed in elderly patients, in the context of age-related sarcopenia or functional loss, and in the vast majority of cases with concurrent calcium supplementation. A number of studies have reported positive functional impacts of vitamin D supplementation on physical performance and risk of falls in the elderly, as reviewed in [29].

Only two studies have to our knowledge examined the effects of vitamin D supplementation on muscle morphology, both in patients with low vitamin D status. In a small, uncontrolled study, *vastus lateralis* biopsies before and after 3-6 months of 1-alpha-hydroxyvitamin D and calcium supplementation were recovered from elderly women suffering from bone loss [35]. Increased succinate dehydrogenase activity, phosphagen levels, as well as an increase in type IIA fiber proportion (at the expense of IIX fibers) and cross-sectional area were noted after the supplementation period. A randomized controlled trial in elderly women with post-stroke hemiplegia (48 supplemented, 48 placebo) taking 1000IU/day of vitamin D2 over 2 years resulted in increased type II fiber diameter and proportion as well as improved muscle strength in the vitamin D-treated group [36]. Positive correlations between type II fiber area and serum 25(OH)D levels were noted before and after treatment in this study. Increased type II fiber area is proposed to account at least in part for increased strength in these studies. However, whether these changes to fiber morphology resulted from direct effects of vitamin D on muscle cells remains unknown, as do the effects of vitamin D supplementation in patients with adequate or normal vitamin D status.

***Although these data suggest that vitamin D supplementation could lead to skeletal muscle morphology or functional changes, these changes are modest and would only be beneficial to patients suffering from statin-induced MRSE.***

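### Objective #2 is sized on MRSE patients (30 v 30), but its outcomes are worded for whole arms of 45 and no contrast is named for the vitamin D question

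*Protocol*

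**What the plan says.** Four statements in the Protocol bear on who is compared in the randomised phase.

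- **Sizing (section 5.0).** The authors calculate that "a total of 60 MRSE suffering patients will be sufficient to demonstrate effects on muscle function by statin withdrawal or vitamin D supplementation", and add that this means 30 per group, one on vitamin D and one on placebo.
- **Arms (section 3.0, Objective #2, Trial design).** "In the experimental group (n=45; 30 with MRSE under statin monotherapy, 15 without MRSE under statin monotherapy from objective #1". The placebo arm has the same make-up.
- **Primary outcomes (section 3.0, Objective #2, Expected findings and outcomes).** One is a smaller functional impact of statins in the supplemented group. The other is "a greater tolerance of statin reintroduction (i.e., fewer self-reported MRSE) in the group receiving vitamin D supplementation". Neither is limited to patients with MRSE.
- **Analysis (section 5.0).** "Statistical analyses will test the comparison of subgroups (with/without symptoms and with/without vitamin D repletion) on the percent change from baseline". For the test itself: "One-way ANOVA will be used to compare means of continuous variables". Proportions go to Chi-square or Fisher's exact test, two-sided at 0.05. The paragraph gives no number of groups, no two-factor model and no named vitamin D contrast.

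The background (section 2.0, on vitamin D and muscle morphology and performance) also says who is expected to gain: "these changes are modest and would only be beneficial to patients suffering from statin-induced MRSE".

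**The concern.** The population that was sized (60 with MRSE), the population in the outcome wording (90 randomised) and the groups in the analysis sentence (formed by two factors) are not the same. The method named has one factor. The text therefore permits three tests of the trial's only randomised question:

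1. vitamin D v placebo among MRSE patients, 30 v 30;
2. vitamin D v placebo among all randomised patients, 45 v 45;
3. one ANOVA across the four symptom-by-arm subgroups, 30/30/15/15.

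These tests answer different questions. The first matches the sizing. The second averages over patients whom the protocol does not expect to benefit. The third asks whether any of four means differ, so a difference between patients with and without MRSE can make it significant even if vitamin D does nothing. Hypothesis 1 in section 1.0 expects patients with MRSE to have reduced strength and increased fatigability. If the choice stays open, it could be made after the data are seen.

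**Working it through.** **Inputs.** Group sizes come from section 3.0 (Table 1 and Trial design), and the two-sided 0.05 level from section 5.0. Means and SDs of percent change come from the preliminary data in section 3.0: nine patients, before and after statin withdrawal. Assumptions: MRSE patients lose on rechallenge what the pilot patients gained on withdrawal, non-MRSE patients lose nothing, and SDs are equal.

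**Step 1: the plan's own figure.** The 30 per group cannot be reproduced, because the target vitamin D effect and the power are not in the text at hand. For orientation only, the pilot changes can be used as a between-arm difference at 80% power, with n per group = 2 × (1.960 + 0.842)² × (SD/difference)². This gives 15.70 × (43/22)² = 60 for extensor strength and 15.70 × (28/17)² = 43 for flexor strength.

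**Step 2: four subgroups in one ANOVA, no vitamin D effect.** Let the 60 MRSE patients have mean −d and the 30 others mean 0. The grand mean is −2d/3, so the noncentrality is λ = [60 × (d/3)² + 30 × (2d/3)²]/SD² = 20 × (d/SD)². The critical value of F(3, 86) is 2.71. Halving d divides λ by 4.

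| Pilot measure | d / SD | λ | P(significant) | at half d |
|---|---|---|---|---|
| Extensor strength | 22/43 | 5.24 | 44% | 13% |
| Flexor strength | 17/28 | 7.37 | 59% | 17% |
| Extensor power | 28/64 | 3.83 | 33% | 11% |
| Flexor power | 29/41 | 10.01 | 74% | 22% |
| Extensor endurance | 28/57 | 4.83 | 41% | 13% |
| Flexor endurance | 20/35 | 6.53 | 54% | 16% |

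In a simulation of the flexor-strength case (40,000 trials), the F test was significant in 59%, the 30 v 30 test in 5.0% and the 45 v 45 test in 4.1%. Only the omnibus test is misleading about vitamin D.

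**Step 3: 45 v 45, effect confined to MRSE.** The arm difference becomes (30 × Δ + 15 × 0)/45 = 2Δ/3.

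- The standardised effect with 80% power at 30 v 30 is 0.736: 0.736/√(2/30) = 2.85 on 58 df.
- Diluted, it is 0.490. Then 0.490/√(2/45) = 2.33, which gives 63% power with adjustment for MRSE. Simulation without adjustment gives 61-62%.
- Restoring 80% would take 15.70/0.490² = 65.3, so 66 per arm.
- If non-MRSE patients gain half the effect, the factor is (30 + 7.5)/45 = 5/6 and power is 82%. If they gain all of it, power is 93%.

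**Step 4: the same with pilot values.** Suppose vitamin D abolishes the whole loss in MRSE patients. With equal SDs, power at 45 v 45 against 30 v 30 is 35% v 50% for extensor strength and 46% v 64% for flexor strength. If non-MRSE patients vary less (SD 15 points, purely assumed), the gap narrows to 46% v 50% and 57% v 64%.

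The tolerance outcome has the same mismatch, but the protocol gives no expected recurrence rates, so no size is attached to it here.

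**The case against.** The strongest reply is that the protocol never states a bad test. Section 5.0 serves both objectives. Symptoms yes or no is the Objective #1 comparison and vitamin D yes or no is the Objective #2 comparison, so the analysis sentence can be read as two separate comparisons. A within-MRSE comparison also fits: the sizing sentence describes it, Table 1 lists it, and the trial design divides patients by MRSE status before randomising. The paragraph that introduces the Objective #2 outcomes speaks first of protecting patients who suffer MRSE. With two groups, one-way ANOVA is simply a t-test and does isolate vitamin D. Comparing all randomised patients is valid too. Finally, a statistical analysis plan or the power appendix, neither at hand, may name the contrast.

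Much of this stands. A reader might infer that the protocol prescribes a four-subgroup omnibus test, or that its vitamin D test is certain to mislead. The documents do not support that, because neither the omnibus test nor the 45 v 45 test is stated. A reader might also infer that patients without MRSE cannot benefit. The background sentence is an expectation, and the same section cites a randomised trial in which vitamin D improved strength in elderly women after stroke.

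The reply does not remove the mismatch. Sizing, outcome wording and analysis sentence point to different groups within the protocol itself. A later plan that chose the 30 v 30 contrast would have to narrow the outcome wording; one that kept that wording would leave the sizing behind. So this is more than detail deferred.

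**Conclusion.** The concern holds as a mismatch within the protocol: the vitamin D comparison is sized on MRSE patients, both primary outcomes are worded for arms in which one third have no MRSE, and no contrast is named. It does not hold as a claim that a wrong test has been prescribed.

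The consequence depends on the reading taken. Within MRSE, there is no problem. At 45 v 45, the false-positive rate is sound, and power falls from 80% to about 62% only if the effect is confined to MRSE patients. With four subgroups in one ANOVA, significance without any vitamin D effect would occur in 33-74% of trials, or 11-22% at half the MRSE difference. The ANOVA figures use SDs from nine patients in an uncontrolled withdrawal pilot and assume that rechallenge reverses the gain. The power figures use assumed effects. They show direction and rough scale, not expected performance. This should be fixed, but it does not invalidate the design: MRSE is a stratification factor, so the within-MRSE contrast is a randomised one.

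**What to change.** In sections 3.0 and 5.0:

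- Name vitamin D v placebo within the MRSE stratum (30 v 30) as the primary Objective #2 contrast for both primary outcomes, so that outcome wording and sizing agree.
- For continuous measures, estimate it as one stated contrast from a model with arm, MRSE status and their interaction. For tolerance, test the proportions in the same stratum.
- Report the 15 v 15 comparison without MRSE and the 45 v 45 comparison of all randomised patients as secondary.
- State that an omnibus F test across the four subgroups will not be used as evidence on vitamin D.

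The cost is wording only. No patients, visits or measurements are added.
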